## Abstract

**Background:**

Frail elderly people need an integrated and coordinated care. The two-armed study "Continuum of care for frail elderly people" is a multi-professional and multidimensional intervention for frail community-dwelling elderly people. It was designed to evaluate whether the intervention programme for frail elderly people can reduce the number of visits to hospital, increase satisfaction with health and social care and maintain functional abilities. The implementation process is explored and analysed along with the intervention. In this paper we present the study design, the intervention and the outcome measures as well as the baseline characteristics of the study participants.

**Methods/design:**

The study is a randomised two-armed controlled trial with follow ups at 3, 6 and 12 months. The study group includes elderly people who sought care at the emergency ward and discharged to their own homes in the community. Inclusion criteria were 80 years and older *or *65 to 79 years with at least one chronic disease and dependent in at least one activity of daily living. Exclusion criteria were acute severely illness with an immediate need of the assessment and treatment by a physician, severe cognitive impairment and palliative care. The intention was that the study group should comprise a representative sample of frail elderly people at a high risk of future health care consumption. The intervention includes an early geriatric assessment, early family support, a case manager in the community with a multi-professional team and the involvement of the elderly people and their relatives in the planning process.

**Discussion:**

The design of the study, the randomisation procedure and the protocol meetings were intended to ensure the quality of the study. The implementation of the intervention programme is followed and analysed throughout the whole study, which enables us to generate knowledge on the process of implementing complex interventions. The intervention contributes to early recognition of both the elderly peoples' needs of information, care and rehabilitation and of informal caregivers' need of support and information. This study is expected to show positive effects on frail elderly peoples' health care consumption, functional abilities and satisfaction with health and social care.

**Trial registration:**

ClinicalTrials.gov: NCT01260493

## Background

The elderly population is increasing, in Sweden as well as in many other countries [1], a trend which is expected to continue [2]. Increasing age often implies increasing frailty, and the oldest old are often described as a frail group. Frail elderly people are at high risk of developing chronic disease, multi-morbidity and functional impairments, which often result in dependence in daily activities [3-7].

Frailty has been recognized as a concept to describe a geriatric syndrome attributable to the multi-system deterioration of the reserve capacity at older ages [8]. The most frequently included characteristics are: mobility, balance, muscle strength, motor processing, cognition, nutrition, endurance and physical activity [3]. Frailty implies a risk of multi-morbidity and thereby a need of care from many care levels and from caregivers with different competences, such as gerontology, geriatrics, internal medicine, rehabilitation, nursing and social work. This makes it clear that frail elderly people need integrated, coordinated care [9].

Integrated care programmes have been used internationally to reduce fragmentation and to improve the continuity and coordination of care. Several programmes have shown positive effects, but it is not clear which components or interventions are essential to these programmes [10]. A review of randomised controlled studies of integrated care programmes for the frail elderly showed that five out of eight studies had positive effects on the elderly person and none had negative effects. Positive effects were reported on medication, client satisfaction, activity of daily living, quality of life and depression [11].

One important component in many of the integrated care programmes is case management. Case management was first implemented in psychiatric care [12,13]. It has also been used to coordinate the care of the elderly [12,14]. Case management has mostly been used in the US, UK, Australia and Italy. Owing to heterogeneity in study design, intervention content, outcome variables and population, the studies are difficult to compare. However, the effects seem to be mainly positive. Some studies have shown positive effects on both the individual and health care consumption, while others have failed to detect any effects [12,14].

Another way to enhance the continuity and integration of the health care of the elderly is geriatric screening and multidimensional assessment at the emergency ward, which has been introduced in many countries. It can be incorporated into practice without too much difficulty. It meets with a high level of acceptance, involves different categories of caregivers and improves the communication between them [15]. Previous research has found that interventions including geriatric nursing assessment and home based services results in functional benefits for elderly high-risk patients. Other key features of trials showing improvement is the selection of patients at high risk of adverse outcomes. One effective strategy is to keep the screening at the emergency ward brief and moving more of the intervention to the patient's home [16]. A systematic review identified that when a multidisciplinary comprehensive assessment was combined with an individually tailored intervention, this promoted functional activity, well-being and life satisfaction [17]. According to a meta-analysis, such interventions are able to decrease readmissions to hospital [18].

In Sweden, "health care chains" have become an important part of integrated health care [19]. A health care chain can be defined as coordinated activities in the health care system, linked together to achieve a final result of good quality for the patient [20]. A well-functioning care chain implies that the care is seen as a continuum running between different caregivers and care levels, and that one caregiver of high quality is not enough to create good care. Elderly frail people meet many different caregivers [21]. Often, the elderly person and their relatives are the only common link between the different care levels [22]. Previous studies have shown that elderly people and their relatives are seldom aware of the different caregivers' responsibilities, and that they have difficulties in knowing to whom turn to concerning different needs [23]. Many relatives experience that they have no influence on the care [24]. In order to achieve a continuum of care, the elderly people and their relatives must be involved in the planning, decision-making and performance of the care [15,25]. A review of randomised controlled studies of integrated care programmes for the frail elderly showed that the two studies that found the most client benefit were ones in which the elderly person was involved [11]. A review of interventions to prevent disability in frail community-dwelling older people points out promising features of interventions to be, for example, multidisciplinary and multi-factorial, individualized assessment and intervention, case management and long-term follow up [26].

The findings from the above-mentioned studies guided us in the design of a multi-professional and multidimensional intervention for frail community-dwelling elderly people, "Continuum of Care for Frail Elderly People". The content of the intervention has been elaborated in collaboration with representatives of the different care levels, i.e. emergency ward, department of geriatrics, department of internal medicine, municipal health and social care, and primary care. The design of the study includes quantitative and qualitative analyses of the effects of the intervention programme as well as of the implementation process, which is followed throughout the whole intervention period.

### Aims and hypothesis

The hypothesis is that this intervention programme for frail elderly people can reduce the number of visits to the emergency ward, increase the satisfaction with health and social care and maintain functional abilities. The overall aim of the study was to implement the intervention and thereby create a continuum of care for frail elderly people, from the emergency ward to their own homes, resulting in a better quality of care and higher cost-effectiveness. Another aim was to study the implementation process of the intervention programme.

This paper presents the study design, the intervention, the outcome measurements and the baseline characteristics of the study participants in accordance with the CONSORT recommendations for reporting pragmatic randomised controlled trials [27].

## Methods/Design

### Project context

The study is part of the research programme "Support for frail elderly persons - from prevention to palliation" (http://www.vardalinstitutet.net) which consists of three different interventions addressing frail elderly people in different phases of the disablement process, from pre-frail to very frail. These interventions address different requirements that arise during the aging process, ranging from health promotion to increasing needs of medical care, nursing, rehabilitation, social care and services and eventually the need of palliative care to promote symptom relief, quality of life, security and satisfaction with care during the final period of life.

The intervention "A continuum of care for frail elderly people" takes place in the municipality of Mölndal, Sweden, including municipal health and social care, the hospital of Mölndal, and primary care. Mölndal is a city situated on the west coast of Sweden, close to the city of Gothenburg. It had nearly 60,000 inhabitants at the beginning of 2009. The population of people aged 65-79 years was 6,289 persons at the beginning of 2009, and the population aged 80 and over was 2,592. In June 2008, 11.6% of the those aged 65 or older received some kind of help or care from the municipality. Mölndal Hospital is part of Sahlgrenska University Hospital, and includes, among others, an emergency ward and departments for internal medicine, geriatrics and orthopaedic care. Sahlgrenska University Hospital has 2300 beds in 165 wards. Twenty-six of these wards are located at Mölndal Hospital. This study includes patients discharged from the emergency ward, internal medicine and geriatrics.

### Study design

The study has a descriptive analytical and experimental design. The intervention is performed as a randomised controlled trial. The participants were randomised to two study arms, one intervention group and one control group. The implementation process is studied and analysed along with the intervention. Explorative interviews are performed with staff and study participants in order to gain an understanding of the intervention and its significance as well as of the implementation. Ethical approval was obtained for the study, ref. no: 413-08, Regional Ethical Review Board in Gothenburg.

### Study population

The study group includes 161 elderly people who sought care at the emergency department at Mölndal Hospital during the period October 2008 to June 2010 and who were discharged to their own homes in the municipality of Mölndal. Inclusion criteria were age 80 and older *or *65 to 79 with at least one chronic disease and dependent in at least one activity of daily living. Exclusion criteria were acute severe illness with immediate need of assessment and treatment by a physician (within ten minutes), dementia (or severe cognitive impairment), and palliative care. The intention was that the study group should comprise a representative sample of frail elderly people at a high risk of future health care consumption.

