### Procedure of the intervention study

The participants were recruited at the emergency wards. The nurse with geriatric competence screened most of the patients during her work shift (daytime, weekdays, approximately 3-4 days per week) to see if they fulfilled the inclusion criteria. If so, the nurse informed them about the study both verbally and in writing. The information included a description of the study, how it would be conducted and what was expected of people who agreed to participate. There were opportunities to ask questions if anything was unclear. It was stressed, both in the verbal and the written information that participation was voluntarily. Of all those invited to participate, 17 were invited by letter, as they had been discharged before the nurse was able to ask them. People who accepted to participate in the study were randomised to intervention or control by using a system of sealed opaque envelopes. All participants signed a written consent form. The study started with a pilot study to test intervention, inclusion/exclusion criteria and logistics. The pilot study comprised the first ten included participants.

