### Statistical analysis and power calculation

A power calculation was done before the start of the study. The calculation was based on the expected relative change over time in functional abilities, i.e. we assumed that the intervention group would change slightly or not at all in their functional status and that the control group would deteriorate by 20% in relation to the intervention group (this assumption was based on clinical experience). Power calculations ensured that we would be able to reveal a difference of at least 20% between the groups, if the hypothesis was true. To be able to detect a difference of at least 20% with a two-sided test and with at significance level of alpha = 0.05 and 80% power we needed at least 95 people in each group. Thus a total of approximately 200 people was planned to be included.

An interim analysis was made to evaluate whether or not the assumed difference evaluation was relevant. This was done with knowledge of more specific prevalence rates of functional abilities which, since the study began, have been gained from the study "Elderly persons in the risk zone" [28]. This knowledge enabled us to make a more detailed power calculation. The prevalence rates were for less frail elderly persons than those in our study. Thus we assumed lower functional status and higher standard deviance. This power calculation was based on the balance scale (one of the primary outcome variables, range 0-56), with an assumed mean for the intervention group of 32 and for the control group of 28 (15% difference), and a standard deviation of 8 in both groups. To be able to detect a difference between the intervention and control groups with a two-sided test and with a significance level of alpha = 0.05 and 80% power we would need at least 65 people in each group.

The analysis will be made on the basis of the intention-to-treat principle, meaning that participants will be analysed on the basis of the group to which they were initially randomised [37]. Both descriptive and analytic statistics will be used to compare the two groups as well as for analyses of changes over time. Non-parametric statistics will be used when ordinal data are analysed. Otherwise, parametric statistics will be used.

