## Discussion

The study "Continuum of care for frail elderly people" was designed to evaluate whether or not a multi-professional and multidimensional intervention targeting frail elderly persons can decrease health care utilization, maintain functional abilities and increase satisfaction with health and social care. One of the major strengths of this study is that the implementation of the intervention programme is followed and analysed throughout the study. This enables us to generate knowledge on the process of implementing complex intervention in health and social care settings, both in term of how the intervention is perceived and translated into practical clinical work and to see what is in the "black box", i.e. to explore how and why different parts of the intervention were/were not implemented. Another major strength is that it has both an explorative and experimental design, facilitating multi-facetted knowledge production. In addition, it is a randomised controlled study, which is very important for the possibility of drawing valid conclusions from the results.

We were not able to include as many frail elderly people as was at first calculated. Still, the 181 included are sufficient enough according to the more detailed interim power calculation, and should be enough even the inevitable attrition in the follow ups. The non-participation rate, 46.8%, is in line with what can be expected for this very frail elderly group of patients, especially as they had to decide whether or not to participate when at the emergency ward with acute symptoms. The median age of the non-participants was somewhat lower than the participants, but the age range was about the same. The most common reasons for not participating were that the study seemed too demanding. There were also a number of persons who were too healthy to see any reason to participate. Thus, there are indications of the non-participants being both healthier and less healthy than the participants. Therefore, the participants can be seen as a fairly representative sample of the frail elderly population.

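### The study group of 161 is described by discharge home, which for admitted patients appears to follow allocation, and it is not reconciled with the 181 reported as included or with intention to treat

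*Protocol article*

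**What the plan says.** Under Procedure of the intervention study: "The participants were recruited at the emergency wards", and then "People who accepted to participate in the study were randomised to intervention or control by using a system of sealed opaque envelopes". One exception to the usual order is given: of those invited, "17 were invited by letter, as they had been discharged before the nurse was able to ask them".

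Under Intervention group, the emergency-ward nurse's assessment goes to the hospital ward and to the case manager, who contacts the ward and patient to start planning the discharge.

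Under Study population, the group is 161 people "who were discharged to their own homes in the municipality of Mölndal". The abstract says the same: "The study group includes elderly people who sought care at the emergency ward and discharged to their own homes in the community". Project context adds the discharging department: "This study includes patients discharged from the emergency ward, internal medicine and geriatrics". The listed inclusion criteria are age or, for the younger group, age with chronic disease and ADL dependence. Discharge destination is not among them.

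Tables 3 and 4 have 76 control and 85 intervention participants. The Discussion says "Still, the 181 included are sufficient enough" when judged against the revised power calculation.

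Under Statistical analysis and power calculation, the principle is intention to treat: "participants will be analysed on the basis of the group to which they were initially randomised".

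**The concern.** Intention to treat protects the comparison only if the analysed set is fixed by allocation and by nothing that happens afterwards. Here the study group is described by an event that, for an admitted patient, cannot be known when consent is given. The intervention works on that same event. If people were randomised and then left out because they were not discharged home, the omission could depend on arm, and the two groups would no longer be comparable by design.

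The two totals make this more than a matter of wording. A reader cannot tell whether 161 or 181 people were randomised, or which number the outcome analysis will use. The comparisons at stake include health care consumption, a primary outcome, and mortality. Both come from registers and need no home visit.

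**Working it through.** **Order of events for an admitted patient**

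1. Recruitment at the emergency ward, with acceptance followed by randomisation (Procedure of the intervention study).
2. In the intervention arm, the case manager starts discharge planning with the ward (Intervention group). This can be part of the allocated intervention only if allocation has already happened.
3. Discharge home, from one of three departments (Study population; Project context).
4. Baseline interview, intended within a week of discharge (Procedure of the intervention study).

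Steps 3 and 4 therefore appear to follow allocation. For people sent straight home from the emergency ward the order is unclear. For the 17 invited by letter, discharge came first.

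**Counts**

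- Tables 3 and 4: 76 + 85 = 161, matching Study population.
- Discussion: 181. Gap: 181 − 161 = 20, and 20/181 = 11.0%.
- Invited (Baseline characteristics): 343. Non-participation would be 1 − 181/343 = 47.2% with 181 participants, or 1 − 161/343 = 53.1% with 161.
- The stated non-participation rate of 46.8% implies 343 × (1 − 0.468) = 182.5 participants. That is close to 181 but matches neither total exactly.
- 161/343 = 46.9%, so 46.8% could also be a participation rate reported the wrong way round. The rate does not settle which total is right.

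**The sample-size figure and what rests on it**

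The revised calculation uses means 32 and 28, SD 8, two-sided alpha 0.05 and 80% power:

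n per group = 2 × (1.960 + 0.842)² × 8² / 4² = 62.8, so 63. The t-test version gives 64. The stated 65 reproduces to within two people.

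- Power for a 4-point difference (normal approximation, before attrition): 88.6% with 76 and 85; 92.0% with 90 and 91 (an assumed split of 181).
- Room for attrition above 2 × 65 = 130: with 181, 51/181 = 28.2%; with 161, 31/161 = 19.3%. The smaller arm of 76 can lose 11 (14.5%) before it falls below 65.

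Both totals exceed the requirement, but the margin for attrition depends on which is right.

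**Possible bias, if 181 were randomised and only 161 analysed**

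Let f be the fraction of an arm that is absent, and δ the mean of retained people minus the mean of absent people on the Berg scale. Then

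bias in (intervention − control) = (f_I − f_C) × δ.

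Neither the arm split of the 20 nor δ is in the document. The range below assumes δ of 4 or 8 points (half or one SD):

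| Absent, control / intervention | f_C | f_I | δ = 4 | δ = 8 |
|---|---|---|---|---|
| 20 / 0 | 20/96 = 0.208 | 0 | −0.83 | −1.67 |
| 10 / 10 | 10/86 = 0.116 | 10/95 = 0.105 | −0.04 | −0.09 |
| 0 / 20 | 0 | 20/105 = 0.190 | +0.76 | +1.52 |

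The signs reverse if absent people function better than retained ones. Against a design difference of 4 points, the bias runs from negligible to about 1.7 points under these assumptions.

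**The case against.** The strongest reply is that the article already states the right principle. Nothing in it says that the outcome analysis uses the 161, or that anyone was removed because of discharge destination. Recruitment had closed, so the phrase about discharge home may only describe the sample. Figure 1, which is not visible here, is said to show the numbers randomised, receiving the allocated intervention and having baseline data, so the reconciliation may be there. The number 181 is called included, not randomised. It could be a misprint, or it could count people who withdrew before allocation. The text also does not say when or where envelopes were opened.

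Most of this is fair, and it limits the point. Several stronger readings are tempting but unsupported:

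- *The analysis is restricted to people with a baseline interview.* This is not stated. It would have to be read from the table totals. Some table percentages fit only smaller denominators (12.2% = 10/82, 40.7% = 33/81, 28.0% = 21/75), so even the 161 do not all have complete data.
- *Follow-up is counted from discharge.* Only the baseline interview is tied to discharge. Table 1 gives no time origin for register outcomes.
- *The absent people are mainly the sickest.* The text gives no reasons for absence after randomisation.
- *The control arm lost more, because 76 is less than 85.* This needs 181 randomised in near-equal arms, which is an assumption. A difference of 9 is unremarkable under simple 1:1 allocation of 161, where the SD of the difference is √161 = 12.7.

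The objection does not remove the conflict within the text. The article sets a study group described by a probable post-allocation event beside an intention-to-treat principle, and it gives two totals. Its adequacy statement rests on the larger total while its tables use the smaller.

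**Conclusion.** The point holds as a conditional one. As written, the description of the study group does not fit the stated intention-to-treat principle, and 161 and 181 are unreconciled in the visible text. If more than 161 people were randomised and outcomes are analysed only in the 161, the analysis is not intention to treat. The gap would then be up to 20 people, or 11.0% of 181.

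This rests on two inferences: that allocation precedes discharge for admitted patients, which the sequence of procedures strongly suggests, and that 181 is the number randomised, which the text does not confirm. If 181 is a misprint, the possible loss of 20 falls away. The sample-size statement would still need correcting, and the discharge-home description would still need clarifying. The document does not establish that biased exclusion occurred.

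**What to change.** 1. Reconcile 161 with 181. Correct whichever is wrong, together with the sample-size statement that relies on it, and check the 46.8% against the corrected count.
2. State the number randomised in each arm, with reasons for absence from the study group by arm.
3. Define the intention-to-treat set as everyone randomised, regardless of discharge destination or whether a baseline interview took place. Say plainly whether discharge home was an eligibility condition or only describes the sample.
4. Analyse the register outcomes (health care consumption and mortality) in all randomised people from the date of randomisation, subject to their consent.
5. For interview outcomes, keep randomised people without data in the denominator and treat them as missing.
6. Label any analysis of the 161 as supportive.

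The cost is revised wording, a register extract for up to about 20 more people and slightly more analysis work. No new visits are needed.
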